## **Appendix 2**

# אישור רישום בפנקס האביזרים והמכשירים הרפואיים

880000

ניתן בזאת אישור, כי בהתאם לבקשת רישום מס :  
האביזרים / מכשירים רפואיים ( אמ"ר ) הבאים :

|                                                                                                                                                                                                                                                                                                                         |                                              |                      |
|-------------------------------------------------------------------------------------------------------------------------------------------------------------------------------------------------------------------------------------------------------------------------------------------------------------------------|----------------------------------------------|----------------------|
| Disposable medical devices - see attached list                                                                                                                                                                                                                                                                          | ציוד רפואי לשימוש חד פעמי - ראה רשימה מצורפת | שם האמ"ר             |
| ראה רשימה מצורפת                                                                                                                                                                                                                                                                                                        |                                              | יעוד האמ"ר           |
| 1. בי"ח - כללי -                                                                                                                                                                                                                                                                                                        |                                              | התויה                |
| ביומטריקס בע"מ ; [name] ; ישראל                                                                                                                                                                                                                                                                      |                                              | שם בעל רישום וכתובתו |
| ביומטריקס בע"מ ; [name] ; ישראל                                                                                                                                                                                                                                                                         |                                              | שם יצרן וכתובתו      |
| ביומטריקס בע"מ ; [name] ; ישראל                                                                                                                                                                                                                                                                         |                                              | שם אתר יצור וכתובתו  |
| התניות                                                                                                                                                                                                                                                                                                           |                                              |                      |
| 
הנחיות
 
- לפי הוראות היצרן שאושרו ע"י גוף המאשר: Intertek 0473
 
- אישור בהתאם לאישור CE ומערכת איכות בתוקף
 
- הערות נוספות: מצורפים לאישור זה 2 דפים נספחים של מוצרים מאושרים.
 
- מאושר לשימוש בהתאם להוראות היצרן כפי שאושרו על ידי הגוף המאשר הנ"ל, לרופא(ה) או אח(ות) בבית חולים בלבד
 |                                              |                      |

נרשמו בפנקס האביזרים והמכשירים הרפואיים במשרד הבריאות  
תוקף האישור לשיווק האמ"ר הינו ליעודים ולהתוויות המתוארים לעיל בלבד  
האישור בתוקף עד: 31/07/2015

27/08/2013

ד"ר [name]  
יחידת האמ"ר

חתימה

תאריך חתימת האישור

שם ותפקיד המאשר

| רשימת מוצרים                                                                                                                | CE Certificate # |
|-----------------------------------------------------------------------------------------------------------------------------|------------------|
| 1. Chest drainage systems:                                                                                           |                  |
| • Reservoirs                                                                                                                | 242 CE           |
| • Drains & catheters: thoracic, trocar, pneumothorax                                                                        | 242 CE           |
| 2. Drainage systems:                                                                                                 |                  |
| • Reservoirs: URX, Bulbs, minivac, prevacuum                                                                                | 242 CE           |
| • Tissue drains (round, flat, fluted including trocars)                                                                     | 242 CE           |
| • Suction tubing and probes                                                                                                 | 242 C CE         |
| 3. Physiological/blood pressure monitoring systems and accessories (including cables):                               |                  |
| • Arterial line                                                                                                             | 242 CE           |
| • ICP                                                                                                                       | 242 CE           |
| • IUP                                                                                                                       | 242 CE           |
| • Intra-abdominal pressure                                                                                                  | 242 CE           |
| 4. Cardioplegia: tubing systems and connectors for cardiopulmonary bypass.                                           | 242 CE           |
| 5. Angio sets & accessories:                                                                                     |                  |
| • PTCA                                                                                                                      | 242 CE           |
| • Cath lab & angio packs                                                                                                    | 242 CE           |
| • Guide wires                                                                                                               | 242 CE           |
| • Manifold sets (systems for contrast media injection including high pressure lines)                                        | 242 CE           |
| • Angiographic syringes                                                                                                     | 242 CE           |
| 6. Infusion and irrigation lines (including tubing sets, stopcocks, connectors, luer activated and infusion needles) | 242 CE           |
| 7. Vascular catheters:                                                                                               |                  |
| • CVC                                                                                                                       | 242 CE           |
| • Dialysis                                                                                                                  | 242 CE           |
| • Arterial                                                                                                                  | 242 CE           |
| • Introducers                                                                                                               | 242 CE           |
| • High flow                                                                                                                 | 242 CE           |

נספח מס' 1 מתוך 2  
לאישור רישום בפנקס האמיר  
מס. 880000

[figure not shown]

|                                                                                       |                 |
|---------------------------------------------------------------------------------------|-----------------|
| 8. Surgical Procedure Packs:                                                   |                 |
| · Drapes, gowns & covers                                                              | 242 CE   |
| · Electrosurgical pencil                                                              | 242 CE   |
| · Surgical instruments (scalpels, forceps etc.)                                       | 242 CE   |
| · Identiloops & silclamps                                                             | 242 CE   |
| · Accessories/ widgets\                                                               | 242 CE   |
| · Ophthalmic surgery instruments                                                      | 242 CE   |
| 9. Electronic measuring devices: FSPM                                          |                 |
|                                                                                       | 242 B CE |
| 10. Drainage catheters: foley, nephrostomy, biliary and more (suprapubic etc.) |                 |
|                                                                                       | 242 CE   |

טבח מס' 2 מתוך 2  
לאישור רישום בפקס האמ"ר  
מס. 88060

[figure not shown]

## **Appendix 3**

## No-charged catheter

[figure not shown]

**hy-labs®**

[figure not shown][figure not shown]

## STERILITY TEST FORM

**Method:** Hy Laboratories SOP No. 10-004

**Technique:** Direct Transfer or Immersion Technique (Only TSB).

**Date Started :** July 16, 2014

**Date of Completion :** July 30, 2014

| Item                      | Lot # | No. of Samples | Sterility Test Results   |                          |                          |                                     |
|---------------------------|-------|----------------|--------------------------|--------------------------|--------------------------|-------------------------------------|
|                           |       |                | Intermediate Results     |                          | Final Results            |                                     |
|                           |       |                | Date                     | Time /                   | Date: 30.07.14           | Time: 11:00                         |
|                           |       |                | Growth                   | No Growth                | Growth                   | No Growth                           |
| Enox Impregnated Catheter | 004   | 1              |  |  |  |  |
| Enox Impregnated Catheter | 004   | 1              |  |  |  |  |
| Enox Impregnated Catheter | 004   | 1              |  |  |  |  |
| Enox Impregnated Catheter | 004   | 1              |  |  |  |  |
| Enox Impregnated Catheter | 004   | 1              |  |  |  |  |
| Enox Impregnated Catheter | 004   | 1              |  |  |  |  |
| Enox Impregnated Catheter | 004   | 1              |  |  |  |  |
| Enox Impregnated Catheter | 004   | 1              |  |  |  |  |
| Enox Impregnated Catheter | 004   | 1              |  |  |  |  |
| Enox Impregnated Catheter | 004   | 1              |  |  |  |  |

**Test Conclusion:**

The Product Complies With the Test: ☒ Yes / ☐ No

GPT of Medium for performing sterility test:

|                                                    |                                 |            |   |   |
|----------------------------------------------------|---------------------------------|------------|---|---|
| Soybean - Caseine Digest
Batch #: 230070 | Bacillus subtilis        | ATCC 6633  | + | + |
|                                                    | Candida albicans         | ATCC 10231 | + | + |
|                                                    | Aspergillus brasiliensis | ATCC 16404 | + | + |
|                                                    | Staphylococcus aureus    | ATCC 6538  | + | + |
|                                                    | Pseudomonas aeruginosa   | ATCC 9027  | + | + |

Negative control of culture Media: TSB: ☐ Growth / ☒ No Growth

Technician: [name]  
Microbiology Technician

Date: July 30, 2014  
 Date: July 30, 2014

Approved by: [name]  
Supervisor

This report is submitted for the exclusive use of the person or corporation to whom is addressed, and neither the report nor the name of these laboratories nor any members of its staff may be used in connection with the advertising, sale or any product or process without the written permission of Hy-Laboratories Ltd. The results are approved for samples tested only.

The use of ISIRAC symbol relates to tests/calibrations which are included in organization scope of accreditation and performance according to the accreditation rules of the tests performance.

ISIRAC is not responsible for the results of the tests performed by the organization/research facility and accreditation/recognition does not constitute a certificate approval of any item, system or process tested

This certificate need to related in full and no part thereof shall be quoted in other documents.

## **Appendix 5**

Possible adverse events related to NO-charged catheters

| No. | Adverse Event                       | Risk analysis                                                                                                                                                                                                                                                                                                                                                                                                                                                                                                                                                                                                                                                                                                                                                                                                                    |
|-----|-------------------------------------|----------------------------------------------------------------------------------------------------------------------------------------------------------------------------------------------------------------------------------------------------------------------------------------------------------------------------------------------------------------------------------------------------------------------------------------------------------------------------------------------------------------------------------------------------------------------------------------------------------------------------------------------------------------------------------------------------------------------------------------------------------------------------------------------------------------------------------|
| 1   | Decrease in systemic blood pressure | In light of the low concentration expected to be released from the catheter (up to 5 ppm NO), and in light of the short half-life of NO in the blood, we believe that such concentration (4-16 fold lower than the concentration given to neonates with pulmonary hypertension) is unlikely to decrease systemic blood pressure. Blood pressure will be assessed 3 times per day during hospitalization (every 8 hours), on catheter removal day, on every unscheduled visit, and 30 days after catheterization.                                                                                                                                                                                                                                                                                                                 |
| 2   | Increased bleeding time             | Blood coagulation tests (Prothrombin Time, Activated Partial Thromboplastin Time, and International Normalized Ratio) will be performed on a routine basis during hospitalization (every day), on catheter removal day, on every un-scheduled visit, and 30 days after catheterization.                                                                                                                                                                                                                                                                                                                                                                                                                                                                                                                                          |
| 3   | Erection                            | A physical examination with emphasis on the genitourinary system (penis, glans, shaft, and prepuce) will be performed on a daily basis during hospitalization, on catheter removal day, on every un-scheduled visit, and 30 days after catheterization.                                                                                                                                                                                                                                                                                                                                                                                                                                                                                                                                                                          |
| 4   | Local irritation                    | 
Biocompatibility of NO-charged catheters was evaluated by several tests conducted in animals: in vivo intradermal reactivity tests, in vivo sensitization test and in vivo safety trial for NO-charged catheters (see appendix 9, 10 and 2, in investigators brochure, respectively). All tests revealed that NO-charged catheter does not trigger dermal reaction in terms of erythema and edema. However, since NO-charged catheters will be used for the first time in human during this trial we have to consider the possibility of local irritation.
 
A physical examination with emphasis on the genitourinary system (penis, glans, shaft, and prepuce) will be performed on a daily basis during hospitalization, on catheter removal day, on every un-scheduled visit, and 30 days after catheterization.
 |

Severe adverse events which are life threatening, and/or can result in prolongation of patient hospitalization, and/or persistent or significant disability, and/or death are not expected in this study.

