### **5.3.2 Laboratory Tests: Blood & Urine**

#### **Blood:**

- Complete Blood Cells Count (CBC).
- Blood biochemistry (electrolytes, renal and liver function tests).
- Coagulation tests (PT, aPTT, INR).

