## 10. RISK ANALYSIS

In light of the low concentration expected to be released from the catheter, and in light of the short half-life of NO in the blood, we do not expect any severe and systemic side effects. However, low concentration of inhaled NO (5-40ppm) in some cases was found to be associated with decreased blood pressure, inhibition of platelet aggregation, and increased bleeding time [38-40]. In addition, NO may trigger local side effects such as erection, local skin irritation, and the formation of skin edema and erythema [41] . (See appendix 5 - table of possible adverse events related to NO-impregnated catheters).

To assess the risk associated with the use of NO-impregnated catheters, ENOX performed a pre-clinical safety study in NZW rabbits. No adverse effect and no safety concerns were raised in the conclusion of this study (see main content of the report in appendix 2 in the investigator brochure). ENOX chose to conduct the safety trial on rabbits and not on larger animals such as pigs for two main reasons: 1) the life habitat of pigs is unsterile by nature and may affect trial outcome, causing undesired manifestations that are not related to NO-impregnated catheters. 2) The anatomy of pigs' urethra is not ideal for catheterization over an extended period

Additional tests performed by ENOX include:

- Mechanical test, performed by degania silicone Ltd., Israel
- In vitro cytotoxicity test performed by Harlan Biotech, Israel (STUDY NO ENI/001/CTX)
- In vivo intradermal reactivity tests performed by Harlan Biotech, Israel (STUDY NO ENI/002/IRT)
- In vivo sensitization test performed by Phycher Bio Developpment, France (Harlan Project NO 41400562)
- In vivo safety trial for the NO-impregnated catheters performed by Harlan Biotech, Israel (STUDY NO ENI/003/EM)

ENOXs NO-impregnated catheter meet with all required criteria and was classified as non-cytotoxic, non-irritating and non-sensitizing device (see full reports in IB).

During the trial catheterized patients will be monitored daily (see protocol, section 6.1) through physical examination and vital signs measurements. In addition, blood tests will also be conducted in order to exclude any significant change in platelet counts, and biochemistry values (see appendix 5 - table of possible adverse events related to NO-impregnated catheters).

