### **11.4.2 Potential Adverse Events Related to NO-impregnated Catheters**

- Bleeding (i.e hemoptysis)
- Decrease in blood pressure
- Erection
- Local irritation

(See appendix 5 - table of possible adverse events related to NO-impregnated catheters).

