**11.4.3 Safety Laboratory Evaluations**

Bleeding test such as prothrombine time (PT), international normalized ratio (INR), activated partial thromboplastin time (aPTT) will be performed (see section 8)

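### The laboratory tests paired with the named platelet and bleeding-time effect of NO do not measure it, and the bleeding adverse event is defined by an airway example

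*Protocol*

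**What the plan says.** Four places in the protocol deal with this hazard.

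- **Section 10 (Risk Analysis)** reports that inhaled NO at 5-40 ppm was in some cases "associated with decreased blood pressure, inhibition of platelet aggregation, and increased bleeding time". It later says that "blood tests will also be conducted in order to exclude any significant change in platelet counts, and biochemistry values".
- **Appendix 5, row 2** lists increased bleeding time as a possible event related to the NO catheter. Its only entry is monitoring: "Blood coagulation tests (Prothrombin Time, Activated Partial Thromboplastin Time, and International Normalized Ratio) will be performed on a routine basis", daily in hospital, at catheter removal, at unscheduled visits and 30 days after catheterization.
- **Section 11.4.3** relabels the same three tests: "Bleeding test such as prothrombine time (PT), international normalized ratio (INR), activated partial thromboplastin time (aPTT) will be performed".
- **Section 11.4.2**, the list of potential related adverse events, has as its first entry "Bleeding (i.e hemoptysis".

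The blood panel in Section 5.3.2 consists of "Complete Blood Cells Count (CBC", biochemistry and "Coagulation tests (PT, aPTT, INR". The schedule in Section 6.2 and the visit lists in Section 8 add no other blood test.

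**The concern.** The hazard as stated concerns how platelets work and how long bleeding lasts. The tests assigned to it give plasma clotting times and, through the count, the number of platelets. If platelets are present in normal number but aggregate poorly, these results can all be normal. Because the protocol pairs the tests with this hazard and calls them a bleeding test, a reader of the study report could take normal values as evidence against it.

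The definition of the bleeding event raises a separate problem. Hemoptysis comes from the airway. After radical prostatectomy with a urethral catheter, the places to expect bleeding are the urinary tract, the area around the catheter and the surgical site, and none of these is named. Section 5.1 makes adverse events associated with the NO catheter a primary safety endpoint, so what the protocol presents as the expected NO bleeding pattern can influence which events are attributed to the device. Safety is the primary objective, and Appendix 5 says this is the first use of the catheter in humans.

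**Working it through.** The protocol gives no figure on this point to reproduce. The check compares its passages; the arithmetic at the end is context only.

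**1. Hazard against measurement**

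| Measure in the protocol | Where | What it gives | Measures platelet aggregation or bleeding time? |
|---|---|---|---|
| PT | 5.3.2, 11.4.3, App. 5 row 2 | clotting time | No |
| aPTT | same | clotting time | No |
| INR | same | standardized PT | No |
| Platelet count | 10 (from the CBC in 5.3.2) | platelet number | No |

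None of the 4 measures addresses the named effect. The wording of 11.4.3 leaves its list formally open, but Sections 5.3.2, 6.2 and 8 schedule nothing further.

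**2. What would still detect bleeding**

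- Section 12 counts any untoward event as an adverse event, whether or not it is thought related.
- Section 11.4.1 collects events from consent through follow-up.
- Sections 5.3.1 and 11.2 provide physical examinations, daily in hospital and at visits, that include penis, scrotum and groin.
- Section 6.2 schedules a CBC at screening, operation, hospitalization, removal and Visit 5.
- Section 13.4 tabulates adverse events and laboratory changes by group.

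Overt bleeding would therefore be recorded.

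**3. How the airway example could change attribution**

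Take hematuria after surgery in a treated patient. Assume that its timing fits catheterization and that surgery readily explains it. Apply the causality rules of Section 12, each of which asks for at least two criteria:

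| Is the event judged to fit the known NO pattern? | Criteria met for unlikely related | Criteria met for possibly related | Result |
|---|---|---|---|
| Yes | 1 of 3 (other explanation) | 2 of 3 (timing, pattern) | Possibly related |
| No | 2 of 3 (other explanation, pattern) | 1 of 3 (timing) | Unlikely related |

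The pattern criterion alone decides the category. Section 12 elsewhere glosses related as possibly or probably. If the endpoint of associated events follows that gloss, the same hematuria counts in one row and not in the other.

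**4. Tables by term**

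Sections 13 and 13.4 present events by system organ class and preferred term, with high level term added in 13.4. Suppose three bleeding terms each show 1 of 6 treated patients. That fits one patient with all three events (1/6) or three patients with one each (3/6). The preferred-term rows do not give the number of patients with any bleeding.

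**5. What 6 treated patients can show**

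- With 0 of 6 events, the exact two-sided 95% upper limit is 1 - 0.025^(1/6) = 0.459.
- The chance of at least one event is 1 - (1 - p)^6. For assumed true rates of 5%, 10% and 20% this is 26%, 47% and 74%. The protocol gives no rate.
- Against 0 of 6 controls, Fisher's exact two-sided p is 0.061 at 4 of 6 and 0.015 at 5 of 6.

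An absence of bleeding would be weak evidence even with a test that matched the hazard.

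**The case against.** The strongest reply is that the protocol does look for bleeding. Bleeding is a listed potential event, and event collection, examinations and blood counts are in place throughout. This stands. A reader might infer that the trial could report no bleeding signal without having looked for one; the documents do not support that.

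A reader might also infer that hemoptysis is the clinical readout. It is not. Section 11.4.2 lists anticipated events and restricts neither collection nor analysis. Its remaining effect is on attribution. Even there, an assessor could look to Section 10 or Appendix 5 and accept any bleeding as fitting the NO pattern. The shift shown in the working is possible, not certain.

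No passage says that normal coagulation results will be taken to exclude an antiplatelet effect, and the stated aim for platelet counts and biochemistry is literally what those tests measure. This also stands. The risk comes from the pairing in Appendix 5 and the label in 11.4.3, not from a declared analysis rule. The hazard itself is qualified: it was reported in some cases with inhaled NO, and the sponsor expects low release and no severe systemic effects.

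Finally, Section 13.4 already covers hemoglobin change and event tables by group, and Section 13 promises individual listings, from which 12 patients can be counted by hand. That limits the gain from a new table. Hemoglobin cannot be the main readout either: Visit 1 is before surgery, so its change includes operative blood loss, and the arms are sequential and non-randomized.

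**Conclusion.** The point holds as a mismatch between a named hazard and its assigned monitoring, together with a badly specified event. None of the 4 laboratory measures addresses platelet function or bleeding time, so normal values cannot support a conclusion on that hazard. The airway example can tip postoperative urinary or surgical-site bleeding from possibly to unlikely related, and so out of the associated events in Section 5.1. This rests on two assumptions: that the assessor takes the NO pattern from 11.4.2, and that associated means possibly or probably related. If such an event led to discontinuation, the tolerability endpoint would be affected in the same way. Capture of overt bleeding is not in doubt. The correction is worth making before the study because safety is the primary objective and the change is small.

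**What to change.** - Reconcile Section 10, Section 11.4.2, Section 11.4.3 and Appendix 5 row 2. State that PT, aPTT, INR and platelet count will not be used to conclude on platelet function or bleeding time.
- In 11.4.2, replace the hemoptysis parenthesis with site-relevant examples, such as hematuria, clot retention, and peri-catheter or surgical-site bleeding.
- Add one pooled table of the number of patients with any bleeding adverse event by arm, regardless of attribution, with the exact 95% interval.
- Show hemoglobin by visit and arm descriptively only. Note that change from Visit 1 includes operative blood loss and that the arms are sequential and non-randomized.

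Whether to add a platelet-function test is for the clinical team. The cost is wording in four places and one table from data already collected. The downside is that the report can no longer cite coagulation tests as excluding this hazard.
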